## **2.1. Primary objectives**

**2.1.1.** To estimate the magnitude and direction of differences between potentially 'disadvantaged' and 'advantaged' groups of patients in their reported MSK health outcomes up to 6 months after consultation [patient-reported outcomes/experiences subcohort]

**2.1.2.** To estimate the magnitude of between-practice variation in rates of primary care (re)consultation, secondary care referral, opioid prescribing, and musculoskeletal imaging for adults consulting with a MSK pain condition [EHR-only processes of care]

## **2.2. Secondary objectives**

**2.2.1.** To estimate differences between potentially 'disadvantaged' and 'advantaged' groups of patients in their experiences of primary care MSK consultation [patient-reported outcomes/experiences subcohort]

**2.2.3.** To explore within-practice change in consultation prevalence and recorded management of MSK pain among adults presenting to general practice over time, including comparing current levels with those before COVID (i.e. pre-2020) [EHR-only processes of care]

**2.2.4.** To plot the flow of patients along different MSK care pathways and to define MSK service organisation characteristics for participating general practices and Primary Care Networks (PCNs) [patient-reported outcomes/experiences subcohort]

**2.2.5.** To produce new benchmarked data on processes and outcomes of care for MSK pain conditions at GP practice and PCN levels and to provide new insights into the credibility, validity, and persuasiveness of new visualisations of this MSK health intelligence and present these for feedback from key stakeholders

**2.2.6.** To explore the relationships between identified variations and inequalities in patient care, outcomes, and experiences and their association with wider determinants and organisational characteristics

**2.2.7.** To test case-mix adjustment methods for identifying outliers for recorded processes of care

**2.2.8.** To evaluate patterns of non-response and non-participation and their implications for bias in the above estimates

### 3 DESIGN

Observational cohort study with 6-month follow-up for self-reported outcomes and 12-month follow-up for EHR outcomes.

### 4 SETTING

General practices in North Staffordshire and Stoke-on-Trent, with the option to extend to additional general practices in the West Midlands (e.g. Wolverhampton).

### 5 ELIGIBILITY CRITERIA

#### 5.1. For general practices

| Inclusion                                                                                                                                                                                                                                                           | Exclusion |
|---------------------------------------------------------------------------------------------------------------------------------------------------------------------------------------------------------------------------------------------------------------------|-----------|
| Located in North Staffordshire or Stoke-on-Trent, (wider Staffordshire / West Midlands if needed) a                                                                                                                                                      |           |
| Uses compatible IT system (e.g. EMIS)                                                                                                                                                                                                                               |           |
| Uses compatible SMS messaging service (e.g. MJog) b                                                                                                                                                                                                      |           |
| Willing and able to undertake regular anonymised medical record audits of MSK consultations during the study period                                                                                                                                                 |           |
| a see section 4 above for circumstances under which widening GP recruitment beyond North Staffordshire & Stoke-on-Trent will be considered
b not required for EHR-only processes of care
MSK Musculoskeletal; SMS Short message service |           |

#### 5.2. For participants

| Inclusion                                                                                                                                                            | Exclusion                                                                                    |
|----------------------------------------------------------------------------------------------------------------------------------------------------------------------|----------------------------------------------------------------------------------------------|
| Patients aged 18 years and above                                                                                                                                     | Inflammatory musculoskeletal disease c                                            |
| Registered with a participating general practice during the study period                                                                                             | Has indicated in the record that they do not consent to be approached about research studies |
| Consulting any primary healthcare professional in the general practice for a painful, non-inflammatory musculoskeletal disorder a during the study period |                                                                                              |
|                                                                                                                                                                      |                                                                                              |

|                                                                                                                                                                                                                                                                                                                                                                                                                                                                                                                                                                                                                   |  |
|-------------------------------------------------------------------------------------------------------------------------------------------------------------------------------------------------------------------------------------------------------------------------------------------------------------------------------------------------------------------------------------------------------------------------------------------------------------------------------------------------------------------------------------------------------------------------------------------------------------------|--|
| Able to provide informed consent b                                                                                                                                                                                                                                                                                                                                                                                                                                                                                                                                                                     |  |
| a according to predefined SNOMED code lists
b patient-report survey component only
c according to predefined SNOMED code lists retrospectively examined over the previous 3 years
NB participating general practices will have the option of screening and excluding potentially eligible MSK consultants whom they deem to be vulnerable or inappropriate to invite for patient-reported outcomes/experiences due to health reasons (e.g. severe mental health condition, significant cognitive impairment, recent diagnosis of terminal illness, nearing end of life) |  |

## 6 STUDY PROCEDURES

### 6.1. Overview

Potential participants will be those consulting a participating general practice for a relevant MSK pain related problem during the study period. Relevant MSK pain-related consultations will be identified using a pre-specified SNOMED codelist. Eligible patients with an active mobile phone number will be invited via SMS text sent from the practice computer system to complete a web-based questionnaire, based on a secure server at Keele University. Patients without an active mobile telephone number at the practice will be posted a questionnaire for pen-and-paper completion via DOCMail, a secure remote document compilation, print and mailing solution. Follow-up questionnaires will be sent by Keele CTU at 3 and 6 months, with a brief questionnaire sent in the intervening months (SMS text or postal). All participants will be asked for informed consent to link their questionnaire responses to primary care electronic health record and healthcare datasets (e.g. hospital visits) held by NHS Digital. This “patient-reported outcomes/experiences subcohort”, providing individual-level, linked patient-reported and health record data, will be used to answer questions on variations in outcomes and experiences of care. Separately, pseudonymised information from primary care electronic health records will also be sought from all eligible patients consulting a participating practice with a relevant MSK pain condition during the study period and across the previous five years. These will be analysed and presented at the level of GP practice and PCN to add a wider, longer-term view of between-practice and between-PCN variation in care.

### 6.2. Strategies to improve inclusion and reduce bias

Participation rates in cohort studies have been declining over several years raising concerns over inefficiency and the potential for selection bias. The use of web-based data collection is increasingly pursued as a low-cost solution to the former problem but may have lower response rates[11] and is still susceptible to selective participation. Internet access in UK households continues to increase year-on-year (96% in 2020[12]) but people most likely to be ‘digitally excluded’ are: older people, people in lower income groups, people without a job, people in social housing, people with disabilities, people with fewer educational qualifications, people living in rural areas, homeless people, people whose first language is not English.[13] These groups may be ‘disadvantaged’ or ‘under-served’[14] and have more complex health needs and poorer outcomes.

The following strategies to improve inclusion and reduce bias are informed by discussions with our Participant Advisory Group, previous synthesis of evidence on the effectiveness of different strategies for survey completion, NIHR INCLUDE[14] and INCLUDE Ethnicity[15] frameworks, previous

experience within the research team, and considerations over what is feasible and affordable for our study.

- Sampling of general practices from across all PCNs in North Staffordshire and Stoke-on-Trent. We will try to over-sample practices in the most deprived neighbourhoods and with a higher proportion of Black, Asian, and minority ethnic patients. To reach a sufficiently diverse population, we will also consider offering study participation to general practices in South Staffordshire and the West Midlands (e.g. Wolverhampton).
- Use of a mixed-mode approach in which those unable or unwilling to complete online questionnaires are offered conventional pen-and-paper self-complete questionnaires.[16] We are not using an explicit 'push-to-web' design (i.e. where web completion is offered as the only mode and alternatives like paper completion are withheld until later on, e.g. for non-respondents).[17]
- The offer of telephone support for questionnaire completion; explicit reassurance that family members can assist (but not substitute) in questionnaire completion for the intended respondent
- The offer of access to a translation service via telephone for study information and questionnaire completion
- Keeping questionnaire length to a minimum[11,18]; presenting questions in a logical order; minimising cognitive burden of questions; explaining where possible the purpose of questions
- Raising awareness of the survey among the practice and registered patient population prior to going live; using reminders to encourage questionnaire completion[11,18]
- Collection of brief information in the questionnaire on important social characteristics (e.g. date of birth, sex, ethnicity, occupational class, financial strain) to help understand participation, care, and outcomes in under-served groups
- Using pseudoanonymised extracts from the GP clinical system to describe the characteristics of those invited to participate (e.g. Practice Code, Practice Name, Age, Sex, Lower Super Output Area (from postcode), Ethnicity, Method of Invite), as well as the characteristics and patterns of care of the total eligible population of MSK consultants to enable evaluation and possible modelling of selective participation

Those who participate in the study and return either a paper or online questionnaire will be given the opportunity to select a local charity that they would like us to make a donation to. At the end of the initial, 3-month and 6-month questionnaires, participants will be given a choice of four local charities to give to. For every returned baseline, 3-month and 6-month questionnaire £1 will be given to the charity specified by the participant.

### **6.3. Patient-reported outcomes/experiences subcohort**

#### **6.3.1. Patient identification and recruitment**

Consecutive eligible patients consulting a participating general practice during the study period will be invited to take part.

##### *Identification of eligible consultations*

When a pre-defined MSK pain-related SNOMED code (symptom or diagnostic code) is entered into the primary care electronic health record, a tag related to the research project will be added to the patient record. Practice staff, supported by the NIHR Clinical Research Network (CRN) where possible, will regularly (typically weekly) run an automated search of their general practice's medical record to identify consulters with a relevant tagged MSK record from the previous week. The automated search includes a screen of the identified patient list to exclude ineligible patients according to exclusion criteria in protocol. GP practices will also have the option of performing a manual screening of the identified list.

##### *Patient invitation*

Using the general practice's existing system for SMS texts to patients identified eligible consulters who have an active mobile phone number on the practice record will be sent an SMS text invitation from the general practice to take part in the research. Identified eligible consulters who do not have an active mobile phone number will be sent an invitation pack via Docmail. The invitation pack will include an invite letter (containing URL link to enable online questionnaire completion if so desired), baseline questionnaire with consent form, return pre-paid envelope and a Participant Information Sheet containing the contact details for Keele CTU should the patient wish to seek more information about the study or seek help to complete the questionnaire.

All potential participants receiving an SMS text invitation will be sent a reminder text approximately 48 hours after the initial text, which will include information on how to contact Keele CTU if they are unable to complete the questionnaire online.

Potential participants who do not respond will receive no further contact and will not be re-invited from the same practice, for example, if they revisit their GP within the study recruitment period.

When potential participants arrive at the online questionnaire, they will be provided with the opportunity to read a Participant Information Sheet and view an information video about the study.

The online questionnaire will be hosted by Keele University, with the option of telephone supported completion from a Keele CTU administrator or translation service. Respondents will be sent a follow-up questionnaire at 3 and 6 months after their initial consultation with a brief questionnaire sent in the intervening months' to capture pain intensity.

Participating GP practice will send an Excel file to the study team on a regular basis (approximately weekly), via NHS.net secure email. This file will contain the Organisational Code, NHS number, anonymised identifier, invite date and method of invitation for each patient sent an invitation to take part in the study. This file will be imported into the Study Management Application by a study administrator. When questionnaires are received into the CTU (online or paper) the information from their consent to take part in the study will be matched to the information from the import file, this will also ensure that the correct patient is taking part in the study.

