### *Brief monthly patient-reported questionnaires*

At months 1, 2, 4, and 5 following the index consultation the patient will be asked one question to report their pain intensity either using SMS text or postal questionnaire. Keele CTU has experience of using 2-way SMS text messages to collect outcome data in previous trials (Foster et al 2017,

Campbell et al 2016). The software development team within the CTU will support this data collection and will make use of an in-house bespoke database-driven Web-based system to manage the sending and receiving of SMS text messages. The participant will respond to Keele CTU via the third-party SMS provider. The CTU system will poll the third-party SMS provider for returned SMS text messages. On processing of returned SMS text messages, the system will import these into the study database and process the response according to the business logic defined in the project. Interception of the original message by a third party would reveal only what the questions were that were being asked, whilst interception of the response would only yield an alphanumeric string.

A telephone number will be provided to enable participants to contact Keele CTU if they have queries relating to the SMS text messaging during office hours.

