### **6.3.4. Data linkage and extraction**

#### *Primary care electronic health record*

Information on comorbidities and MSK management, including those needed to address the primary objective, will be collected from the primary care electronic health record. This will include relevant prescription medications, referrals to other services (e.g., physiotherapy and secondary care specialists), referrals for investigations (e.g., radiographs, MRI/Computerized Tomography (CT) scans), sick certifications (fit notes), and further MSK-related primary care consultations.

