## 7.2. Planned recruitment rate

The rate of patient recruitment for the patient reported outcomes per practice is detailed above. The overall rate of patient recruitment to this study will depend on when each practice begins patient recruitment. Due to practice circumstances, CTU and CRN capacity, we anticipate a staggered start for practices over a 3-month period (**Table 2**).

**Table 2.** Planned recruitment rate, by month

| Month                                                                                                                 | 1   | 2    | 3    | 4    | 5    | 6 |
|-----------------------------------------------------------------------------------------------------------------------|-----|------|------|------|------|---|
| No. of GP practices recruiting                                                                                        | 8   | 17   | 26   | 18   | 9    | - |
| Cumulative eligible adult MSK consultants                                                                             | 584 | 1825 | 3723 | 5037 | 5694 | - |
| Cumulative no. of participants completing baseline questionnaire a                                         | 146 | 456  | 931  | 1259 | 1424 | - |
| a Does not account for lag between consultation and completion of baseline questionnaire (est. average 2w) |     |      |      |      |      |   |

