#### **7.3.1.2 Primary outcomes analysis**

We will report summary statistics (mean and standard deviation, median and interquartile range) for the MSK-HQ baseline, 3-month and 6-month score and its mean change over 3- months and 6- months overall and stratified by age, gender, and type of musculoskeletal pain. We will also determine the percentage of patients who achieve the minimal important change (MIC) for the MSK-HQ. This has been reported as 6 points, though varies by body region of pain. We will weight responses by age, gender, and type of musculoskeletal pain at baseline.

We will determine patient characteristics associated with baseline MSK-HQ score using multilevel linear regression models (patients nested within practices) including as covariates the key case-mix variables.

To assess inequalities in change in musculoskeletal health over the 6-months, we will use multilevel repeated measures linear regression models (follow-up measures nested within patients) to determine patients characteristics associated with MSK-HQ score at 3m and 6m, adjusting for baseline MSK-HQ score and the case-mix variables.

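### Follow-up is timed from the index consultation, but the described practice file carries only the invite date and baseline falls about two weeks after time zero

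*Protocol*

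**What the plan says.** Primary objective 2.1.1 concerns outcomes up to 6 months after consultation, and the schedule is anchored to match. Section 6.3.1 (Patient invitation) states: "Respondents will be sent a follow-up questionnaire at 3 and 6 months after their initial consultation". Section 6.3.3 (Brief monthly patient-reported questionnaires) states: "At months 1, 2, 4, and 5 following the index consultation the patient will be asked one question". Table 1 and sections 6.1 and 8.1 give months without an anchor.

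The same part of section 6.3.1 describes the weekly file that practices send for import into the Study Management Application: "This file will contain the Organisational Code, NHS number, anonymised identifier, invite date and method of invitation for each patient". The consultation date is not listed there, and Table 1 has no such item.

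Baseline comes after the consultation. Practices search about weekly to "identify consulters with a relevant tagged MSK record from the previous week", then invite, then wait for a reply. The footnote to Table 2 in section 7.2 says of the recruitment counts: "Does not account for lag between consultation and completion of baseline questionnaire (est. average 2w"). No spread, no upper limit, and no breakdown by group or invitation mode is given.

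Section 7.3.1.2 summarises the MSK-HQ score and "its mean change over 3- months and 6- months overall", plus the percentage reaching a 6-point MIC. It then models patient characteristics "associated with MSK-HQ score at 3m and 6m, adjusting for baseline MSK-HQ score and the case-mix variables". Section 7.3.1.3 models MIC achievement as a secondary analysis. None of these mentions the lag.

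**The concern.** There are two linked problems.

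First, the protocol fixes a time origin and describes a data feed that does not contain it. Whoever sets the mailing dates must use the invite date or the date of the baseline return, and the protocol does not say which.

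Second, the baseline score is taken partway through the episode. A patient who improves between consultation and questionnaire enters with a better baseline and shows less change, so is less likely to count as reaching the MIC. If one social group returns its questionnaire later than another, adjusting for baseline makes the later group look worse at 3 and 6 months even when the true courses are identical. Section 6.3.1 gives a route for this: SMS invitees get a link and a reminder at about 48 hours, while no baseline reminder is described for postal invitees. Section 6.2 notes that the digitally excluded overlap with potentially disadvantaged groups, and objective 2.1.1 compares exactly such groups.

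**Working it through.** **The plan's own figure.** Eligible patients per practice-month: 7300 × 0.80 × 0.15 / 12 = 73. Cumulated over 8, 17, 26, 18 and 9 practices this gives 584, 1825, 3723, 5037 and 5694. Multiplying by 0.25 gives 146, 456, 931, 1259 and 1424, so Table 2 reproduces. As its footnote says, the lag does not enter these counts.

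**Timing, from the 2-week average.** Take 3 months as 91.3 days, 6 months as 182.6 and one month as 30.44.
- Share of the interval before baseline: 14/91.3 = 15.3% at 3 months and 14/182.6 = 7.7% at 6 months.
- Baseline to follow-up: (91.3 − 14)/30.44 = 2.54 months and (182.6 − 14)/30.44 = 5.54 months.
- The month-1 pain question falls 30.44 − 14 ≈ 16 days after baseline.
- For an assumed lag of 1 to 4 weeks the shares are 7.7% to 30.7% and 3.8% to 15.3%.
- If mailings ran from baseline completion instead, they would fall (91.3 + 14)/30.44 = 3.46 and (182.6 + 14)/30.44 = 6.46 months after consultation.

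**Effect of a uniform 2-week lag on the MIC rate (illustration).** The protocol gives no recovery curve, so the gains and curve shapes here are assumptions. Section 7.1.1 gives SD 10 and correlation 0.5, so the SD of change is 10 × √(2 × (1 − 0.5)) = 10. The curves are scaled to reach the total gain at 26 weeks.
- Gain 6, linear recovery: points lost 6 × 2/26 = 0.46. The MIC rate falls from 50.0% to 1 − Φ(0.046) = 48.2%.
- Gain 10, half-life 4 weeks: points lost 10 × (1 − 2^(−2/4))/(1 − 2^(−26/4)) = 2.96. The MIC rate falls from 65.5% to 54.1%.
- The range is about 2 to 11 percentage points.

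**Effect of a lag that differs by group (illustration, identical true courses).** Assume a total gain of 6 and lags of 2 and 4 weeks. The gain remaining at baseline is 6 × 2^(−L/h), with lag L and half-life h in weeks. The baseline-adjusted bias is the slope of 0.5 times the baseline difference.

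| Half-life (weeks) | Remaining gain, lag 2 v 4 | Difference in raw change | Baseline-adjusted bias |
|---|---|---|---|
| 2 | 3.00 v 1.50 | 1.50 | 0.75 |
| 4 | 4.24 v 3.00 | 1.24 | 0.62 |
| 8 | 5.05 v 4.24 | 0.80 | 0.40 |

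- At a half-life of 4 weeks the MIC rates would be 43.0% v 38.2%.
- The table gives one whole group the longer lag. If only the postal share differs between groups, the effect shrinks in proportion. With an assumed 20-point difference, 1.24 × 0.20 = 0.25 raw and 0.12 adjusted. With 40 points, 0.50 raw and 0.25 adjusted.
- Lags of 1 v 3 weeks, gains of 6 to 10 points and half-lives of 12 to 4 weeks give 0.79 to 2.49 raw and 0.40 to 1.25 adjusted.

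The 3-point follow-up target in section 7.1.1 is baseline-adjusted, so the adjusted column is the one to compare with it.

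**The case against.** Much of the case on the other side stands.

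- A reader might infer that the study team never obtains the consultation date. The protocol does not show that. Section 6.3.4 says: "Information on comorbidities and MSK management, including those needed to address the primary objective, will be collected from the primary care electronic health record", and further MSK consultations are among the extracted items. The index date is not named, and extraction would probably be too late for scheduling, but it could serve the analysis for consenting patients.
- A reader might infer that the schedule cannot be run at all. With weekly searches of the previous week, the invite date is normally within about a week or so of the consultation, which is tolerable for the 3- and 6-month points. The text also describes the file as a means of matching patients, not as the source of mailing dates.
- A reader might fear that a month-1 question reaches someone before a late baseline. It cannot: follow-up goes to respondents, and consent and contact details come with the baseline questionnaire (sections 6.3.1 and 6.3.2). A late baseline could at most miss that slot.
- Early change is not wholly unmeasured. Table 1 lists a global rating of change at month 0, although its reference period is not stated and it does not recover the MSK-HQ at consultation.
- Measuring follow-up from the consultation serves objective 2.1.1. The main model uses follow-up scores adjusted for baseline, which reduces the effect; mean change is descriptive and the MIC model is secondary.
- Lag covariates and sensitivity runs are ordinary SAP content, and the SAP is not at hand.

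The last point does not dispose of the matter. An SAP cannot repair mailing dates, and a lag covariate needs a date that no described source names.

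**Conclusion.** The mismatch between the stated time origin and the described data feed stands on the protocol's text. It also follows from the protocol's own 2-week estimate that about 15% of the 3-month and 8% of the 6-month interval precede baseline, so the change scores and MIC rate describe a shorter and later stretch than their labels suggest.

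The bias in the group comparison is conditional. It needs a lag that differs by group, which is a reasonable inference from SMS versus postal invitation, but the documents give no lag by group or mode. With a 2-week difference in lag and the assumed recovery curves it is roughly 0.1 to 0.75 points, rising to about 1.25 with larger assumed gains, against the 3-point target. Setting the raw change differences of 0.8 to 1.5 points against that target would overstate it, because the follow-up target is for a baseline-adjusted score.

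This is a cheap improvement worth making. It does not show that the primary comparison is unsound.

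**What to change.** 1. In section 6.3.1, add the index consultation date to the weekly practice file, and state that every monthly, 3-month and 6-month mailing is scheduled from it.
2. Section 6.3.2 already has baseline consent dated, with the date of receipt as fallback on paper. Use that date with the consultation date to derive days from consultation to baseline.
3. Include this lag as a covariate, or in a sensitivity analysis, in the 3- and 6-month MSK-HQ and MIC models of sections 7.3.1.2 and 7.3.1.3.
4. Report the lag by social group and invitation mode, so that readers can see whether it differs.

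The cost is one extra column in an existing file, one covariate and a small protocol amendment. The change makes the stated schedule workable and the lag visible. It cannot recover the MSK-HQ score at consultation, which is never taken in a design that identifies patients from the record afterwards.
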